### Blinding

This study is an open-label trial.

### The classification of ultrasound biomicroscopy-based angle closure

Patients who have been diagnosed with PAC will be invited to undergo a UBM examination (SW3200L®; Suowei Electronic Company, Tianjin, China). The UBM examination will be conducted at every center by a technician with at least 3 years’ experience in operating a UBM machine and who has also received training according to the standard operating procedures of the study. The UBM examination will be performed in a dark room with illumination of ≤ 5 Lux. Images of the four quadrants (the superior, inferior, nasal, and temporal quadrants) and one image of the central anterior chamber will be acquired in supine subjects.

The criteria for acceptable images will be clear visualization of the scleral spur, angle, ciliary body, and the half chord of the iris. After obtaining the UBM results, the research physicians will upload the UBM images (containing anonymized information) to an online computer system that is only accessible to the UBM analysts, who will send the classification results on to the research physician after reviewing the images and determining the results according to the UBM classification criteria. The UBM analysts will consist of three glaucoma specialists. Every UBM figure will be read by at least two specialists. If agreement on the results cannot be reached by the two specialists, a third will be approached in order to obtain consensus.

The UBM classification criteria are as follows [5, 16]:
*Iris convexity:* judged according to the curvature of the posterior surface of the iris, the iris bombe is defined as the location of the posterior surface of the iris above a line drawn from the iris root to the iris margin of the pupil (Fig. 2a).

**Fig. 2 Fig2:**
[figure not shown]
UBM-based angle closure configuration classification. **a** Thickening of the peripheral iris; **b** iris bombe; **c** anterior rotation of the ciliary body. *UBM* ultrasound biomicroscopy
*Thickness of the peripheral iris:* the thickness of the peripheral iris will be graded with reference to limbal corneal thickness and is defined as greater than half the thickness of the limbal zone of the cornea (Fig. 2b).
*Anterior rotation of the ciliary body:* the anterior rotation of the ciliary body will be judged according to the direction of the axis of the ciliary body in the anterior position, with the disappearance of the ciliary groove (Fig. 2c).

Thus, there will be seven configurations (combinations) of angle closure, as defined according to the aforementioned criteria, including:The iris bombe.Thickening of the peripheral iris.The anterior rotation of the ciliary body.The iris bombe plus thickening of the peripheral iris.The iris bombe plus the anterior rotation of the ciliary body.Thickening of the peripheral iris plus the anterior rotation of the ciliary body.The iris bombe plus thickening of the peripheral iris, plus the anterior rotation of the ciliary body.

Multiple mechanisms of angle closure are defined as combinations of two or three factors including the iris bombe, thickening of the peripheral iris, and the anterior rotation of the ciliary body.

Regarding the quadrants, the configuration of angle closure in one eye is defined as at least two quadrants belonging to one configuration; if two quadrants belong to one kind of configuration, and the other two belong to another kind of configuration, thereafter, reference will be made to the contralateral eyes.

### Intervention description

#### Single laser peripheral iridotomy

LPI will be performed using a VISULAS® 532 s diode laser (Carl Zeiss Meditec, Dublin, USA). Thirty minutes prior to the procedure, a drop of 2% pilocarpine will be instilled into the eye every 15 minutes. Topical anesthesia will be administered. The selected treatment site will be the superior nasal iris or iris crypt, where present. Treatment will be initiated with a pulse of 3–5 mJ. The power will be increased until patency is achieved and the opening of the iris is > 0.1 mm. Patency will be determined by direct visualization of the posterior chamber.

#### Laser peripheral iridoplasty plus laser peripheral iridotomy

LPIP will be applied using a VISULAS® 532 s diode laser (Carl Zeiss Meditec). Thirty minutes prior to the procedure, a drop of 2% pilocarpine will be instilled into the eye every 15 minutes, Topical anesthesia will be administered. Twenty to 30 ms spots of 250–300 mW power, measuring 300–500 microns, will be applied for a duration of 400–500 ms. Power will be modified arbitrarily until an effective iris contraction is obtained. Effective iris contraction will be considered to constitute concentric movement around the laser spot, with minimal iris pigmentation and immediate angle opening, as observed through a Goldmann® lens mirror. Power will be lowered if a bursting sound is perceived, or in the event of pigment dispersion, air bubbles, or considerable pain. LPI will be performed after the LPIP procedure is complete.

### Primary outcome measures

The PAC progression rate will be determined by the number of patients in whom the disease progresses following laser treatment in each group within the 3-year follow-up period. PAC progression is defined as the presence of any of the following:Acute angle-closure crisis.An IOP measurement taken 1 month after the laser procedure that is 8 mmHg higher than that recorded at treatment initiation.An IOP measurement taken 1 month after the laser procedure that is ≥ 22 mmHg when measured three times in succession.The progression of PAS ≥ 1 clock hour within 3 years of the laser procedure, as determined by gonioscopy.Glaucomatous neuropathy within 3 years of the laser procedure.

Acute angle-closure crisis is defined as:The presence of at least two of the following symptoms: ocular or periocular pain, nausea and vomiting, blurred vision, and multicolored halos around lights (an occasional symptom).An IOP measurement of at least 22 mmHg, as measured by Goldmann® applanation tonometry.The presence of at least three of the following signs: conjunctival injection, corneal edema, a mid-dilated unreactive pupil, and a shallow anterior chamber.

Glaucomatous neuropathy is defined as:The documented progression of diffuse thinning and focal narrowing or notching of the optic disc rim.A cup disc ratio of ≥ 0.6.A cup-disc asymmetry ratio of ≥ 0.2 for similar-sized eyes or optical discs.Diffuse or localized abnormalities in the peripapillary retinal nerve fiber layer.The presence of glaucomatous visual field defect, defined as reproducible visual field defects, including nasal step, arcuate field defect, or paracentral depression in the clusters of the test sites.Visual field loss in the upper hemifield that is different to that in the lower hemifield.The absence of any other known explanation.

### Secondary outcome measures

Secondary outcome measures include the following:Determining, through the administration of a questionnaire, whether or not additional medication (to control IOP) or additional surgery is required to control the progression of PAC.Establishing whether or not there are any changes in the best-corrected visual acuity after the laser procedure.Determining the number of corneal endothelium cells.Establishing any change in the angle width and configuration, as measured by UBM.

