## Abstract

**Background:**

China has the largest burden of primary angle-closure glaucoma (PACG) worldwide. The mechanism of the angle closure is complex and includes pupillary block and non-pupillary block. Currently, opinion is that laser peripheral iridotomy (LPI) alone is not sufficient to prevent disease progression. Laser peripheral iridoplasty (LPIP) is an alternative and effective way of widening the angle recess in eyes that are affected by primary angle closure (PAC). However, it is not known if greater benefit would be achieved using LPI plus LPIP for PAC with multiple mechanisms (MAC). Thus, the aim of this study is to demonstrate if LPI plus LPIP would be more effective than single LPI in controlling the progression of PAC with multiple mechanisms, based on ultrasound biomicroscopy (UBM) classification. A secondary aim is to determine whether or not this would result in the use of less medication and/or prolong the time to antiglaucoma surgery.

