**Discussion:**

If the LPI plus LPIP is found to significantly decrease the rate of PAC progression, this intervention could potentially be a standard therapy to be used to treat PAC when multiple mechanisms are involved in angle closure. Subsequently, this would have the potential to delay the rate of PAC progression to PACG and delay the time to the administration of antiglaucoma medication or trabeculectomy surgery.

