## Methods

### Study objective

The aim of this study is to demonstrate the efficacy of LPI plus LPIP versus LPI in reducing the rate of 3-year disease progression in patients with multiple mechanisms of angle closure based on UBM classification. A secondary objective is to assess the safety of LPI plus LPIP in the study population over its duration.

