### Data collection and monitoring

All data will be collected at the scheduled follow-up times (Table 1). Trained clinical research associates at each center will examine the data on the patient information sheet, all of which will be entered into a trial-specific online database, Research Electronic Data Capture®. The data manager will monitor the data in a timely manner to control the quality of the data. Access to the final dataset will be limited to the trial administrator and the statistician.

**Table 1 Tab1:** Schedule of visits and examination items

Visit number	1	2	3	4	5	6	7	8	9	10	11	12
Examination item	-7 to -1 day	Laser day	1 W (±1 D)	1 M (±1 W)	3 M (±1 W)	6 M (±1 W)	1 Y (±2 W)	1½ Y (±2 W)	2 Y (±2 W)	3 Y (±2 W)	4 Y (±2 W)	5 Y (±2 W) EOS
Informed consent	X											
Demographics data	**X**											
Medical history	**X**											
Vital signs	**X**	**X**										X
Height and weight	**X**											
Medication record	**X**		X	X	X	X	X	X	X	X	X	X
Refraction	**X** ^**b**^			X		X	X	X	X	X	X	X^**b**^
Visual acuity	**X** ^**b**^		X	X	X	X	X	X	X	X	X	X^**b**^
Slit lamp biomicroscopy	**X** ^**b**^		X	X	X	X	X	X	X	X	X	**X** ^**b**^
Fundus examination	**X** ^**b**^			X		X	X	X	X	X	X	**X** ^**b**^
IOP (Goldmann)	**X** ^**b**^	**X** ^**b**^	**X** ^**b**^	**X** ^**b**^	**X** ^**b**^	**X** ^**b**^	**X** ^**b**^	**X** ^**b**^	**X** ^**b**^	**X** ^**b**^	**X** ^**b**^	**X** ^**b**^
A scan	**X** ^**b**^						X		X	X	X	**X** ^**b**^
Endothelial cell count	**X** ^**b**^			X		X	X		X	X	X	**X** ^**b**^
UBM	**X** ^**b**^			X		X	X	X	X	X	X	**X** ^**b**^
AS-OCT	**(X** ^**b**^ **)**			(X)		(X)	(X)	(X)	(X)	(X)	(X)	**(X** ^**b**^ **)**
Humphrey 24-2	**X** ^**b**^				X		X		X	X	X	**X** ^**b**^
Antiglaucoma surgery				X	X	X	X	X	X	X	X	X
Laser treatment		X										
Adverse event	**X**	**X**	**X**	**X**	**X**	**X**	**X**	**X**	**X**	**X**	**X**	**X**

X^b^: examination item for both eyes; (x): optional examination item (AS-OCT)

*EOS*, the end of the study, *IOP* intraocular pressure, *UBM* ultrasound biomicroscopy, *AS-OCT* anterior segment optical coherence tomography, *W* week, *M* ﻿month, *Y* year

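### The questionnaire outcome on medication or surgery carries no amount and no time, so it does not measure the abstract's aim of less medication or later antiglaucoma surgery, although Table 1 schedules records that could

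*Protocol article*

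**What the plan says.** All references are to the protocol article.

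- **Abstract, Background.** The secondary aim is to determine "whether or not this would result in the use of less medication and/or prolong the time to antiglaucoma surgery".
- **Abstract, Discussion.** If progression is reduced, the combined laser treatment might "delay the time to the administration of antiglaucoma medication or trabeculectomy surgery".
- **Study objective (Methods).** After the efficacy objective on 3-year progression: "A secondary objective is to assess the safety of LPI plus LPIP in the study population over its duration". Medication use and time to surgery are not mentioned.
- **Secondary outcome measures.** Of the four items, one touches the aim. It begins "Determining, through the administration of a questionnaire" and asks "whether or not additional medication (to control IOP) or additional surgery is required to control the progression of PAC". The other three are visual acuity, corneal endothelial cells, and angle width and configuration.
- **Data collection and monitoring, Table 1.** The row "Medication record" is marked at visit 1 and at every visit from 1 week onward. The row "Antiglaucoma surgery" stands on its own and is marked at every visit from 1 month onward. No row is labelled as a questionnaire.
- **Data analysis.** The methods named are t tests, Wilcoxon tests, chi-square or Fisher's exact test, logistic regression and a generalized linear model. No time-to-event method is named.

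**The concern.** An aim can be met only by an outcome measured on the same scale. Less medication needs a quantity, and a longer time to surgery needs an event time. The listed outcome supplies neither: it records whether further treatment was needed.

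At stake is what the trial can report on its secondary aim. With the outcome as defined, and the categorical tests that the article names for such data, the result is a difference in proportions. Two arms in which the same share of patients reach surgery, but at different times, would look identical. Two arms in which the same share use drops, but different numbers of them, would also look identical. If time-based or count-based outcomes are added only once results are known, they will be open to the charge of having been chosen afterwards.

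**Working it through.** **1. The plan's own figure.** The only calculation in the article is the primary sample size. Inputs (Sample size; Randomization process): 55% v 35%, two-sided 5%, 80% power, 1:1, 20% loss.

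n per arm = [1.960 × √(2 × 0.45 × 0.55) + 0.842 × √(0.55 × 0.45 + 0.35 × 0.65)]² / 0.20² = (1.379 + 0.580)² / 0.04 ≈ 96.

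96 / 0.80 = 120 per arm, 240 in total. The stated figure reproduces and does not bear on this point.

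**2. Aim against outcome.**

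| Element of the aim | What it needs | Listed outcome | Table 1 |
|---|---|---|---|
| Less medication | Number of drugs, or time to first drug | Whether required; no count, no date | Medication record at every post-laser visit |
| Longer time to antiglaucoma surgery | Time from laser to surgery | Whether required; no date | Separate surgery entry from 1 month |

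No other listed outcome fills either gap.

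**3. Why a proportion cannot show a delay.** Suppose that, with complete follow-up to τ = 36 months, a share p of each arm has surgery, at mean times m₁ and m₂ among those who have it.

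- Difference in proportions: p − p = 0, whatever m₁ and m₂ are.
- Mean event-free time up to τ in arm i: τ − p(τ − mᵢ).
- Difference in mean event-free time: p(m₂ − m₁), which is not zero if surgery is delayed.

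In this situation a log-rank test can also miss the delay. An early excess of events in one arm is offset by a later excess in the other, and the curves meet at 3 years. A restricted mean comparison is therefore needed beside it. The difference is scaled by p, so it will be small if surgery is rare.

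**4. How finely Table 1 would date an event.** Surgery entries to 3 years fall at 1, 3, 6, 12, 18, 24 and 36 months. If only the visit is known, the intervals are 1, 2, 3, 6, 6, 6 and 12 months wide. The medication record adds a 1-week visit. This is coarse late in follow-up, but enough to estimate time to event; recorded dates would remove the limit.

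**5. Starting point for drug use.** Under Inclusion criteria, patients already on antiglaucoma medication undergo washout before randomization. Time from laser to first IOP-lowering drug therefore has a clear origin.

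**6. Precision.** The documents give no surgery or medication rate, so power for this aim cannot be derived from them. As an assumed range, a two-sided 5% comparison of proportions with 96 per arm has these powers:

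| Assumed 3-year rates | Power |
|---|---|
| 10% v 5% | 26% |
| 20% v 10% | 49% |
| 30% v 15% | 70% |

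Better outcomes make the aim estimable. They do not make it well powered.

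**The case against.** The strongest reply is that the data exist. Table 1 records drugs and surgery separately at successive visits, and a fuller protocol or analysis plan may define the derived outcomes. That stands against one tempting reading, that the aim cannot be answered at all: it can be, from the scheduled records. It does not remove the mismatch, because the article does define an outcome for this subject, and on a different scale from its own aim.

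A reader might infer more than the text supports in four other places.

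- **A merged endpoint.** The outcome joins medication and surgery with 'or', but never says that they are pooled, and Table 1 keeps them apart. A composite is one reading. On the other, each item is still without amount or time.
- **An unsupported planned conclusion.** The abstract's Discussion is conditional on reduced progression and speaks only of potential. It is a remark on implications and not a result that the trial undertakes to show.
- **Recall bias.** The article does not say who completes the questionnaire or that it relies on memory, and the medication and surgery rows may be filled from it. Bias of this kind cannot be asserted from the text.
- **A contradiction in the objectives.** The Methods name safety as a secondary objective, without saying that it is the only one. The aim is omitted there, not contradicted.

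'Whether or not' is also the article's habitual phrasing, used for visual acuity and for the aim itself, so it need not mean a strict yes/no variable. Even so, neither count nor timing is specified.

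**Conclusion.** The point holds in this form: the secondary outcome as defined does not measure the secondary aim as stated. Following the article as written would give neither a delay to surgery nor a reduction in drug use.

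The defect is one of definition, not of data collection. It is limited to one secondary aim; the primary outcome, its analysis and N = 240 are untouched. No numerical effect can be attached to it, because the documents give no medication or surgery rates.

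The conclusion rests on the article's own wording and assumes that no other document already defines these outcomes. If one does, the article's outcome list should be brought into line with it. The change is worth making because it is cheap and the records are already scheduled.

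**What to change.** Align the abstract's aim, the Study objective section and the Secondary outcome measures section. Replace the questionnaire item with separate outcomes taken from the Table 1 records:

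1. Time from laser to first antiglaucoma surgery.
2. Time from laser to first IOP-lowering drug.
3. Number of IOP-lowering drugs in use at the 3-year visit.

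Summarise outcomes 1 and 2 to 3 years with Kaplan-Meier curves, a Cox or log-rank comparison, and the difference in restricted mean event-free time. Report drugs and surgery separately. Record event dates where possible, so that timing does not depend on visit spacing.

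If this is not adopted, remove the wording about prolonging time to surgery from the aim, and state the medication part as whether medication is needed.

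**Cost.** This needs wording changes and a few more secondary analyses. No new visits or examinations are needed, and the sample size does not change. Timing will be interval-wide if exact dates are not recorded, and estimates for surgery will be imprecise if it is rare.

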### Safety evaluation

An evaluation of the safety of the procedures, including any laser-related complications and adverse events, will be conducted and will cover:
*Corneal injury:* corneal injury will be sought via an examination by slit lamp and by conducting a corneal endothelium cell count.
*Anterior uveitis:* inflammation in the anterior chamber is indicative of anterior uveitis.
*Changes in the pupil:* any changes to the pupil will be established following an examination by slit lamp.
*Lens injury:* lens injury will be determined following an examination by slit lamp.
*Retinal injury:* a fundus examination will be conducted to evaluate whether or not retinal injury has occurred.
*Blindness:* blindness will constitute a major adverse event.

### Data collection and monitoring

All data will be collected at the scheduled follow-up times (Table 1). Trained clinical research associates at each center will examine the data on the patient information sheet, all of which will be entered into a trial-specific online database, Research Electronic Data Capture®. The data manager will monitor the data in a timely manner to control the quality of the data. Access to the final dataset will be limited to the trial administrator and the statistician.

**Table 1 Tab1:** Schedule of visits and examination items

Visit number	1	2	3	4	5	6	7	8	9	10	11	12
Examination item	-7 to -1 day	Laser day	1 W (±1 D)	1 M (±1 W)	3 M (±1 W)	6 M (±1 W)	1 Y (±2 W)	1½ Y (±2 W)	2 Y (±2 W)	3 Y (±2 W)	4 Y (±2 W)	5 Y (±2 W) EOS
Informed consent	X											
Demographics data	**X**											
Medical history	**X**											
Vital signs	**X**	**X**										X
Height and weight	**X**											
Medication record	**X**		X	X	X	X	X	X	X	X	X	X
Refraction	**X** ^**b**^			X		X	X	X	X	X	X	X^**b**^
Visual acuity	**X** ^**b**^		X	X	X	X	X	X	X	X	X	X^**b**^
Slit lamp biomicroscopy	**X** ^**b**^		X	X	X	X	X	X	X	X	X	**X** ^**b**^
Fundus examination	**X** ^**b**^			X		X	X	X	X	X	X	**X** ^**b**^
IOP (Goldmann)	**X** ^**b**^	**X** ^**b**^	**X** ^**b**^	**X** ^**b**^	**X** ^**b**^	**X** ^**b**^	**X** ^**b**^	**X** ^**b**^	**X** ^**b**^	**X** ^**b**^	**X** ^**b**^	**X** ^**b**^
A scan	**X** ^**b**^						X		X	X	X	**X** ^**b**^
Endothelial cell count	**X** ^**b**^			X		X	X		X	X	X	**X** ^**b**^
UBM	**X** ^**b**^			X		X	X	X	X	X	X	**X** ^**b**^
AS-OCT	**(X** ^**b**^ **)**			(X)		(X)	(X)	(X)	(X)	(X)	(X)	**(X** ^**b**^ **)**
Humphrey 24-2	**X** ^**b**^				X		X		X	X	X	**X** ^**b**^
Antiglaucoma surgery				X	X	X	X	X	X	X	X	X
Laser treatment		X										
Adverse event	**X**	**X**	**X**	**X**	**X**	**X**	**X**	**X**	**X**	**X**	**X**	**X**

X^b^: examination item for both eyes; (x): optional examination item (AS-OCT)

*EOS*, the end of the study, *IOP* intraocular pressure, *UBM* ultrasound biomicroscopy, *AS-OCT* anterior segment optical coherence tomography, *W* week, *M* ﻿month, *Y* year

### Data analysis

The statistical tests will be two-sided. A level of 0.050 will constitute statistical significance. A comparison of the normally distributed continuous variables between two groups, expressed as mean ± standard deviation, will be determined using two independent *t* tests. The natural logarithmic transformation will be applied to variables that are positively skewed. Non-normally distributed continuous variables, presented as the median and interquartile range, will be analyzed using the Wilcoxon rank-sum test. The ordinary variables, also presented as median and interquartile range or percentages, will be analyzed using Wilcoxon signed-rank test. Pearson’s chi-square test or Fisher’s exact test will be used, as appropriate, for the categorical data and expressed as percentages. If the primary outcome is not realized, the last observation carried forward method will be used to impute the reason why. Any other values will remain as absent. The baseline characteristics will be evaluated using intent-to-treat (ITT) analysis. Efficacy analysis will be applied to the ITT and per protocol populations. Reasons for loss to follow-up will also be presented.

An evaluation of the rate of disease progression after 3 years of follow-up will be conducted using efficacy analysis as the primary outcome measure. A comparison in this regard will be made between the LPI and LPI plus LPIP groups using Pearson’s χ^2^ test. Logistic regression analysis will be performed to evaluate the central effect and the progression rate adjusted to account for it.

The safety evaluation data, as per the secondary outcome, will be analyzed using a generalized linear model in consideration of any covariates or the central effect. Sensitivity analysis will be conducted to assess for heterogeneity. Statistical Analysis Software® 9.4 (SAS Institute Inc., Cary, NC, USA) will be used to analyze the collected data. The data analysis will be performed by personnel in the Department of Biostatistics, Southern Medical University, Guangzhou, China.

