### Trial design

This study has been designed as a 3-year, multicenter, randomized, parallel group, open-label, superiority trial. Interim analysis will not take place during this study. A completed Standard Protocol Items: Recommendations for Interventional Trials (SPIRIT) checklist for the trial is available (see Additional file 1).

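### The Wilcoxon signed-rank test, a paired test, is assigned to ordinal variables although the two arms are independent

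*Protocol article*

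**What the plan says.** The Data analysis section assigns a test to each type of variable in consecutive sentences:

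- Normal continuous variables: "A comparison of the normally distributed continuous variables between two groups" is done by an independent-samples t test ("will be determined using two independent" *t* tests).
- Non-normal continuous variables: these "will be analyzed using the Wilcoxon rank-sum test".
- "The ordinary variables, also presented as median and interquartile range or percentages": these "will be analyzed using Wilcoxon signed-rank test".
- Categorical variables: Pearson's chi-square or Fisher's exact test.

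The word *ordinary* is read here as *ordinal*; nothing else fits a class that sits between continuous and categorical.

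Trial design describes a "3-year, multicenter, randomized, parallel group, open-label, superiority trial". Inclusion criteria allow one study eye per patient.

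On baseline, Secondary outcome measures lists "any changes in the best-corrected visual acuity after the laser procedure", a change in UBM angle width and configuration, and the number of corneal endothelial cells. Safety evaluation lists the endothelial count again, under corneal injury. For safety data, tied by the same sentence to the secondary outcome, Data analysis says that they "will be analyzed using a generalized linear model in consideration of any covariates or the central effect".

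**The concern.** The signed-rank test ranks within-pair differences. It needs two measurements on the same unit, or matched units. The rank-sum test, named one sentence earlier, is the version for independent samples. The article gives the two tests to different variable types, so an analyst who follows the text literally would use the paired test where there are no pairs.

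The document states a wrong rule here; it does not merely leave a detail to a later plan. The trial is open-label, so the test for each outcome type is better fixed in advance than corrected silently once data are available. At stake is the interpretability of the ordinal comparisons, not the primary result.

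A second, lesser matter is precision. The t test for continuous variables names no baseline covariate, although Table 1 collects baseline visual acuity, endothelial count and UBM.

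**Working it through.** **1. The plan's own figure, to fix the group size.** Sample size assumes progression of 55% and 35%, two-sided 5%, 80% power and 20% loss. With pooled proportion 0.45:

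n = [1.960·√(2·0.45·0.55) + 0.842·√(0.55·0.45 + 0.35·0.65)]² / 0.20² = (1.379 + 0.580)² / 0.04 ≈ 95.9, so 96 per arm.

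96 / 0.8 = 120 per arm, 240 in total. This reproduces the stated number exactly. The checks below use 96 evaluable patients per arm.

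**2. Are there pairs across arms?** Parallel-group randomization and one eye per patient mean that each patient contributes to one arm only. No matching is described, so there are no pairs.

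**3. Signed-rank run across arms with arbitrary pairing.** The article gives no ordinal distributions, so a five-level outcome was assumed: probabilities 0.40, 0.25, 0.20, 0.10, 0.05 in one arm and 0.54, 0.22, 0.14, 0.07, 0.03 in the other; 2,000 runs.

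| | Rank-sum | Signed-rank, arbitrary pairs |
|---|---|---|
| Type I error (both arms on the first distribution) | 0.049 | 0.050 |
| Power | 0.52 | 0.46 |

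In one data set, re-pairing the same values 2,000 times gave signed-rank p-values from 0.023 to 0.172 (central 95%: 0.041 to 0.115). The rank-sum test gives one value, 0.080. Whether the result falls below 0.05 then depends on the order of the records. With unequal numbers of evaluable patients, some would also have no partner.

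**4. Signed-rank run within each arm against baseline.** The same true change was assumed in both arms (27% better, 60% unchanged, 13% worse). In 47% of 2,000 runs one arm was significant and the other was not. For two arms with equal power p this rate is 2p(1−p), at most 50%, so the assumed change is close to the worst case. The logical point does not depend on it: two separate before-after tests are not a test of the difference between treatments.

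**5. Efficiency from baseline (secondary point).** Let ρ be the correlation between baseline and follow-up, with equal variances at both times. The variance of the treatment effect from a baseline-adjusted linear model is 1−ρ² of that of a t test on follow-up values, and (1−ρ²)/[2(1−ρ)] = (1+ρ)/2 of that of a t test on change scores. Dividing 96 by the ratio gives the number per arm that the unadjusted test would need for equal precision.

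| ρ (assumed) | vs follow-up: 1−ρ² | per arm | vs change: (1+ρ)/2 | per arm |
|---|---|---|---|---|
| 0.3 | 0.91 | 105 | 0.65 | 148 |
| 0.5 | 0.75 | 128 | 0.75 | 128 |
| 0.7 | 0.51 | 188 | 0.85 | 113 |
| 0.8 | 0.36 | 267 | 0.90 | 107 |

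**The case against.** The strongest reply is that this is a slip of wording. The correct rank-sum test appears one sentence before, *ordinary* is itself a slip, and the signed-rank sentence does not say that it compares groups. No outcome is labelled ordinal, so the reach may be small. Most of this is fair, and it is why the consequence is limited. It does not rescue the sentence: its neighbours are all between-group tests, no within-patient analysis is described anywhere, and the text gives the two Wilcoxon tests to different variable types.

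A reader might infer that the resulting p-values are meaningless. That is too strong. With arbitrary pairing the type I error stayed near 5% in the simulation; what is lost is reproducibility and some power.

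A reader might also infer that the plan ignores baseline for continuous secondary outcomes and so weakens the detection of endothelial cell loss. The document does not support this. Visual acuity and angle width are defined as changes, and a t test on change uses baseline. The endothelial count is a safety item, and safety data go to a generalized linear model that allows covariates. The covariate list may sit in an analysis plan that is not shown, and an unadjusted t test between randomized arms is valid. What remains is that the endothelial count, as both a secondary outcome and a safety item, falls under two stated methods, and the text does not say which governs.

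**Conclusion.** The signed-rank assignment is wrong as written and should be corrected. This rests on the design alone: independent arms and no pairs. It assumes only that *ordinary* means ordinal and that the sentence, like those around it, concerns the comparison of arms.

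The consequence is confined to ordinal secondary or safety variables, which the article does not list. The numerical illustrations (p from 0.023 to 0.172, power 0.46 against 0.52, 47% discordant within-arm results) depend on assumed distributions and show the kind of problem, not its size in this trial. The primary chi-square test, the logistic model, the significance level and the total of 240 are untouched.

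The baseline point is a recommendation for precision, not an error. For the two outcomes defined as changes, the relevant ratio is (1+ρ)/2, between 0.65 and 0.90 over the assumed range of ρ. The larger gains against follow-up values apply only if follow-up values alone were tested.

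**What to change.** In Data analysis, replace *ordinary* with *ordinal*, and replace the signed-rank test with the Wilcoxon rank-sum test for between-arm comparisons. Optionally use its van Elteren form stratified by the randomization IOP stratum, or a proportional-odds model. If a signed-rank test is wanted to describe within-patient change, say so and state that it is not a comparison of treatments.

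As an optional improvement, analyse visual acuity, angle width and endothelial count by a linear model with arm, baseline value and IOP stratum as covariates, in line with the generalized linear model already named for safety data. State which method governs the endothelial count.

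The cost is wording only, in a dated change made before the data are analysed. Table 1 already schedules the baseline measurements, and no extra patients, visits or data are needed.
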